### Participants

#### Inclusion criteria

Participants will meet the following criteria: (1) being 65 years of age or older; (2) exhibiting symptoms of depression with a score of ≥4 on the self-rated 15-item Geriatric Depression Scale (GDS-15); and (3) reporting that they eat meals alone in the questionnaire.

The study will include individuals with sub-threshold depression. Indicated prevention aimed at sub-threshold depression is said to be most efficient in terms of costs and benefit [26]. As there are no agreed-upon definitions of sub-threshold depression on GDS-15, the study will include those with scores ≥4 points on the GDS-15, which is 1 point below the established cutoff to detect major depression [27].

Considering the nature of the intervention, the study will target those who are at risk of social isolation. We hypothesize that eating alone, rather than living alone, better represents the risk of isolation. In fact, eating alone was more strongly associated with depression than living alone among community-dwelling older adults [28].

#### Exclusion criteria

Participants will be excluded if they cannot understand and sign the informed consent form. Those who currently reside in a hospital or institution will be excluded.

### Sample size

To detect an effect size of 0.5 with *P* = 0.05 at 80% power, 63 participants are required per group. Assuming a non-consent and dropout rate of 30%, a total of 180 subjects are needed. Based on the results of our previous observational study performed in the same town in 2012, this sample size is believed to be feasible.

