**Methods/Design:**

This is a pragmatic, non-blinded, parallel comparison, randomized controlled trial using Zelen’s design in a community setting. Participants will include community-dwelling older adults (aged 65 years or older) with limited social support (indicated by eating meals alone) and with symptoms of depression (scoring 4 or higher on the 15-item Geriatric Depression Scale (GDS)). The intervention will consist of sending postcards with handwritten messages and seasonal reports from a historical city to participants once a month for eight consecutive months. Self-addressed, stamped envelopes will be enclosed to facilitate non-obligatory replies. Primary outcomes will be changes in the GDS scores that are administered to all elderly inhabitants of the community every year as part of annual health checks. Secondary outcomes include quality of life as measured by a visual analogue scale, and self-rated basic and advanced activities of daily living. We will also examine the subjective sense of effectiveness of the intervention, recollection of the number of intervention mailings received, and the number of mailed replies as the index of the acceptability of the postcard intervention. The time × group interaction for two consecutive years will be analyzed using a generalized linear mixed model. To detect an effect size of 0.5 at alpha error of 0.05 and statistical power of 0.80, 63 participants per group are required. Based on an estimated consent and dropout rate of 70%, a total of 180 subjects will be recruited.

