### Study design

#### Design overview

We will conduct a pragmatic, non-blinded, parallel comparison, randomized controlled trial using Zelen’s design in this community. Figure 1 depicts the participants’ flow. Participants will be selected based on the questionnaire surveys including a self-rated depression scale. Participants will then be randomized to the intervention or no-intervention groups at a 1:1 ratio using computer-generated random numbers. Randomization will be stratified by gender and self-rated depression scale score. To conceal group assignments, random number generation and group allocation will be conducted at the same time by an independent epidemiologist not involved in the participant recruitment or intervention or assessments. Informed consent forms will be mailed to those assigned to the intervention group. Postcards will be sent to the consenting participants once a month for eight consecutive months. They will be enclosed with a self-addressed stamped envelope to facilitate non-obligatory replies by mail. As this is a pragmatic study, any treatment outside the trial will be permitted. Self-reported outcomes will be measured at baseline and post intervention; the questionnaire about participants’ impression of effectiveness of the intervention and their recollection of the number of postcards received will be measured after treatment.

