#### Zelen’s design

The study uses a randomized controlled trial with the single consent version (Zelen’s design) [23,24]. This is a variation of the standard randomized controlled design in which participants are randomized to intervention or control before consent is sought. Consent is obtained from the intervention group only after the randomization. The most important advantage of this method is that participants know the intervention they will receive at the time of consent. In a conventional randomization, participants who agree to join the study may retract their consent or continue participation with reluctance after finding out their assigned intervention, whereas the Zelen’s method requires a decision only on the allocated intervention.

The main ethical concern is that consent is obtained only from the intervention group. To overcome this point, the revised Zelen method has been proposed [25]. This method is a combination of an observational study and a randomized controlled trial. Eligible participants first consent to an observational study, and then they are randomly assigned to intervention and control groups; those in the intervention group are asked to consent to participate in the study. Those in the control arm are not informed of this, but will be followed in the observational study if they agreed. Our protocol will follow this method.

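### The sample size counts refusal of the letters as lost data in both arms; in this single-consent Zelen design refusal dilutes the effect, so power by randomised arm may be below 80%

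*Protocol article*

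**What the plan says.** The Sample size section starts from a standardised effect of 0.5: "at 80% power, 63 participants are required per group". It then adds one allowance for two kinds of loss: "Assuming a non-consent and dropout rate of 30%, a total of 180 subjects are needed". The split between them is not given. The Abstract gives the same total with the allowance worded differently: "Based on an estimated consent and dropout rate of 70%, a total of 180 subjects will be recruited".

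Allocation is equal: "Participants will then be randomized to the intervention or no-intervention groups at a 1:1 ratio using computer-generated random numbers". The section on Zelen's design fixes when consent is sought and from whom: "Consent is obtained from the intervention group only after the randomization". That section adds that eligible people first agree to the observational study, and that controls are not told of the intervention and are followed through that study. According to the Design overview, letters go only to those in the intervention arm who consent. According to the Abstract, the GDS is given every year to all elderly inhabitants as part of the health check. The Statistical analysis section compares the groups through a time-by-group interaction and contains no rule that removes refusers.

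**The concern.** Refusal and dropout act on power in different ways here. Dropout removes outcome data and can occur in both arms. Refusal can occur only in the intervention arm, because controls are never asked. A refuser has already been randomised, belongs to the observational cohort and can still be measured at the annual check, but gets no letters. In a comparison by randomised arm, such a person stays in the intervention arm with no expected benefit and pulls the mean difference towards zero.

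The calculation treats both as attrition and applies the combined rate to both arms. It therefore credits the control arm with a loss that the design rules out, and makes no allowance for dilution in the intervention arm. At stake is the power figure by which a null result would be read. If true power by randomised arm is nearer 70% than 80%, a non-significant result says less about the letters than the plan implies.

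**Working it through.** **Inputs.** From the Sample size section and the Abstract: effect 0.5 (SD = 1), alpha 0.05, power 0.80, 63 per group, 30% combined non-consent and dropout, 180 in total. From the Design overview: 1:1 allocation. Sidedness is not stated; two-sided is assumed, because it reproduces 63 (one-sided gives 50).

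**Step 1: reproduce the plan.** n = 2(1.96 + 0.8416)² / 0.5² = 2 × 7.849 / 0.25 = 62.8, so 63 per group. Then 63 / 0.7 = 90 per arm, and 180 in total. The stated figures reproduce. The exact t-test gives 79.5% at 63 per arm, so that is the baseline for the table below.

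**Step 2: separate refusal from loss.** Let c be the share of the intervention arm that refuses and r the share of each arm with a follow-up GDS.

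- Effect by randomised arm: (1 − c) × 0.5 + c × 0 = 0.5(1 − c), with SD kept at 1.
- Analysed number per arm: n = 90r.
- Power: two-sided t-test with 2n − 2 degrees of freedom and noncentrality 0.5(1 − c) × √(n/2).

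The document does not say how the two losses make up 30%, so two conventions are shown. Additive: r = 1 − (0.30 − c) = 0.70 + c. Multiplicative: r = 0.70 / (1 − c).

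Worked case, c = 10%, effect 0.45:

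- Additive: n = 90 × 0.80 = 72, noncentrality 0.45 × √36 = 2.70, power 76.5%.
- Multiplicative: n = 90 × 0.778 = 70, noncentrality 0.45 × √35 = 2.66, power 75.3%.

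| Refusal c | Effect by arm | n per arm (add. / mult.) | Power (add. / mult.) | Effect in recipients detectable at 80% (add. / mult.) |
|---|---|---|---|---|
| 0% | 0.500 | 63 / 63 | 79.5% | 0.50 |
| 5% | 0.475 | 67.5 / 66.3 | 78.2% / 77.5% | 0.51 / 0.52 |
| 10% | 0.450 | 72 / 70 | 76.5% / 75.3% | 0.52 / 0.53 |
| 20% | 0.400 | 81 / 78.75 | 71.6% / 70.4% | 0.55 / 0.56 |
| 30% | 0.350 | 90 / 90 | 64.6% | 0.60 |

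The reason is that noncentrality is proportional to effect × √n. Losing 30% of the subjects multiplies it by √0.7 = 0.84; 30% refusal multiplies it by 0.70.

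**Step 3: drop the refusers instead.** About 63 consenters are then compared with 63 to 90 controls. Nominal power at 0.5 is about 80–86%. This sets self-selected consenters against all controls, and is no longer the randomised comparison.

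**Step 4: read 0.5 as the effect over everyone randomised.** With refusers retained, n runs from 63 to 90 per arm and power from about 80% to 92%. The effect among recipients would then have to be 0.5 / (1 − c): 0.56 at 10% refusal and 0.71 at 30%.

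**The case against.** **The shortfall is conditional.** A reader might infer that 180 subjects definitely miss 80% power. The document does not support that. It does not say to whom 0.5 applies, how the 30% splits, or which set is analysed, and a condensed article may leave the last to the analysis plan. It makes outcome data for refusers likely but does not say outright that they are followed. This objection stands. Against it, the calculation applies 0.5 to the 63 left after non-consenters are removed, which fits an effect among recipients better than one over everyone randomised.

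**The loss may be small.** At 5% refusal it is 1 to 2 points from the 79.5% baseline. The 65% end needs all 30% to be refusal and no dropout, which sits badly with a rate that names both. This stands, and is why the full range is given.

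**The planned model is not a plain t-test.** Use of baseline data could recover power. With an assumed baseline-to-follow-up correlation of 0.5, ANCOVA would give about 77% at 30% refusal and 86% at 15% (additive split). A change-score contrast would gain nothing at 0.5; at 0.6 it would give about 84%, 80% and 74% at 10%, 20% and 30% refusal (multiplicative split). But no correlation is stated and the plan's calculation claims no such gain. Dilution also remains: ANCOVA at 0.5 would have 90% power with no refusal, against 77% at 30%.

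**The Abstract's 70%.** Read literally as loss, it would require 63 / 0.3 = 210 per arm. The Abstract's own total of 180 rules that out. It is a slip of wording for the share retained, and adds no weight to the main point.

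**Conclusion.** The point holds in conditional form. The arithmetic is correct for its inputs; the fault is that one rate merges two quantities that act differently, and applies refusal to an arm that cannot refuse. The stated 80% is therefore not established for the comparison by randomised arm.

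If 0.5 SD is the effect among recipients, refusers gain nothing and are analysed as randomised, and a plain two-sided t-test is used, power at 180 is about 77–78% at 5% refusal, 75–77% at 10%, 70–72% at 20% and 65% at 30%. The shortfall is slight at 5% and material from about 10%. Neither alternative reading vindicates the calculation. Dropping refusers keeps nominal power at the cost of randomisation. Taking 0.5 over everyone randomised makes the inflation for non-consent unnecessary.

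A reader might go on to infer that the treatment estimate is biased. The document does not support that: with refusers kept in their arm, the issue is power and how a null result is read.

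**What to change.** Keep 180. In the Sample size section:

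1. State the expected refusal rate (intervention arm only, dilutes the effect) and the expected loss to follow-up (both arms, reduces n) separately, and say how they combine.
2. Say whether 0.5 is the effect among letter recipients or over everyone randomised.
3. State that the comparison is by randomised arm with refusers retained, and restate the power, or the effect detectable at 80%, for that analysis under the chosen split. Any gain claimed from baseline data needs a stated correlation.

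As a minor editorial change, align the Abstract's 70% with the 30% non-consent and dropout of the Sample size section.

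The change is to wording and needs no extra participants and no new procedure. Its cost is a stated power that, if 0.5 refers to recipients, is likely to be less favourable.

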### Intervention

Letters written on A4 paper with some colorful illustrations will be sent in a sealed envelope once a month for 8 months. The letter will be composed of two parts: the first part will be a handwritten reply to messages returned from the participants if there are replies or comments, which aims to increase social connectedness and to enhance their self-respect; the second part will be seasonal greetings or news of the month from Kyoto, Japan, where the study authors are located, printed by computer. Kyoto is one of the most famous cultural centers in Japan and hosts various historical events that we believe will be of interest to participants living far from Kyoto.

Although a self-addressed stamped reply card will be enclosed with the letter, replying is not mandatory; this will be indicated on the reply card.

### Outcomes

#### Primary outcomes

Primary outcomes will be the change in GDS-15 score as the measure of effectiveness.

#### Secondary outcomes

Secondary outcomes will be self-rated QOL as evaluated by visual analogue scales, self-rated basic ADL, and self-rated advanced ADL.

#### Other outcomes

The subjective sense of effectiveness of the intervention, recollection of the number of intervention mailings received, and the number of mailed replies will be evaluated to measure acceptability of the postcard intervention.

### Outcome measures

#### GDS-15

The GDS-15 is a validated depression scale comprised of 15 items. This scale was developed to exclude the effects of non-specific somatic symptoms such as anorexia and insomnia, which are frequently observed among elderly populations [29,30]. Each item can have two answers: yes or no. The highest possible score is 15, indicating the most severe depressive state. Using a cutoff point of 5, the GDS-15 has a sensitivity of 92% and a specificity of 81% to detect major depression as ascertained by a structured clinical interview [27].

#### QOL

Subjective QOL will be assessed using a 100-mm visual analogue scale (lowest QOL on the left end of the scale, and highest on the right) for the following five items: subjective sense of health; relationship with family; relationship with friends; financial state; and subjective happiness [31,32].

#### Basic ADL (BADL)

Each participant will rate his or her independence with respect to seven items corresponding to basic activities of daily living (BADL). Specifically, these items are as follows: walking, ascending and descending stairs, feeding, dressing, going to the toilet, bathing, and grooming. Each BADL item is evaluated based on four levels of competence: 3, completely independent; 2, requiring some assistance; 1, requiring much assistance; 0, completely dependent. The scores for the seven BADL items will be summed for a total score of 0 to 21 [33,34].

#### Advanced ADL (AADL)

For higher-level functional capacity, the Tokyo Metropolitan Institute of Gerontology Index of Competence rating scale will be used to measure competence [35,36]. This scale consists of 13 items encompassing three sublevels of competence: (1) instrumental ADL (five items: the ability to use public transport, buy daily necessities, prepare a meal, pay bills, and handle banking matters); (2) intellectual activities (four items: the ability to complete forms, read newspapers, read books or magazines, and show interest in television programs or news articles on health-related matters); and (3) social roles (four items: the ability to visit friends, give advice to relatives and friends in confidence, visit someone at the hospital, and initiate conversation with younger people). Because each item is rated as ‘yes’ or ‘no’, instrumental ADL has a score range of 0 to 5, intellectual ADL 0 to 4, and social role ADL 0 to 4.

#### Sociodemographic and other information

Data about age, sex, eating alone, and living alone will be obtained through a self-reported questionnaire. Participants’ subjective sense of the effectiveness of the intervention will be evaluated on a four-point scale ranging from 0 (not effective) to 4 (very effective).

### Management of adverse events

We expect that no adverse events will result from the postcards. However, if an emergent situation such as a high risk of suicide is suspected based on the reply card, a certified psychiatrist will evaluate the participant and refer him/her to the hospital if needed.

### Statistical analysis

The time × group interaction for baseline and post intervention will be analyzed using a generalized linear mixed model, which enable us to analyze data even when they have missing values. Sensitivity analysis will be conducted by way of ANCOVA with data imputed by a multiple imputation method and with completer’s data, using baseline data alone or with ADL score as a covariate and post-intervention data as dependent variables. The homogeneity of variance will be analyzed with Leven’s test. Statistical analysis will be performed using SPSS ver. 20.0 (IBM Inc., Armonk, NY, USA).

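### The main analysis is in effect a change-score comparison that does not condition on baseline GDS-15; promoting the baseline-adjusted analysis already planned would gain precision at no cost

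*Protocol article*

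**What the plan says.** All references are to the protocol article.

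- **Primary outcomes**: the outcome is change in GDS-15.
- **Statistical analysis**, main analysis: "The time × group interaction for baseline and post intervention will be analyzed using a generalized linear mixed model". No covariate is named. The reason given for the mixed model is that it can use incomplete data.
- **Statistical analysis**, sensitivity analysis: ANCOVA on the post-intervention score, with multiply imputed and with completer data. The covariate is the baseline value, either alone or together with ADL score.
- **Design overview**: "Randomization will be stratified by gender and self-rated depression scale score".
- **Inclusion criteria**: entry requires a baseline GDS-15 of 4 or more.
- **Sample size**: "at 80% power, 63 participants are required per group", for a standardised effect of 0.5, then "Assuming a non-consent and dropout rate of 30%, a total of 180 subjects are needed". Neither this section nor the abstract ("To detect an effect size of 0.5 at alpha error of 0.05 and statistical power of 0.80") says whether 0.5 is in SDs of the score or SDs of the change.

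**The concern.** With one baseline and one follow-up value, a time × group interaction fitted with free main effects is the difference in mean change. That amounts to fixing the regression slope of follow-up on baseline at 1. People who enter because they scored above a threshold tend to regress to the mean, so the true slope is likely to be below 1, and the fixed slope then leaves explainable variation in the error term.

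Randomisation is also balanced on GDS score. A test that does not condition on GDS score computes its standard error as if that balance had not been arranged, so its interval is wider than it should be.

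At stake is the precision of the primary result in a trial of 126 evaluable people from one town. The analysis that would recover this precision is already written into the plan, but only in second place.

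**Working it through.** **Inputs.** From the article: effect size 0.5, alpha 0.05 (two-sided assumed, since sidedness is not stated), power 80%, 63 per group, 1:1 allocation, 30% non-consent and dropout, 180 in total. Assumed: the correlation r between baseline and follow-up GDS-15, shown for 0.3 to 0.7.

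**1. The plan's own figure.** n per group = 2(1.960 + 0.842)²/0.5² = 62.8, so 63. Total = 126/(1 − 0.30) = 180. Both figures reproduce under the normal approximation. An exact t-test gives 63.8, and 79.5% power at 63, which is an immaterial difference.

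**2. Change score against ANCOVA, equal variances σ².**
- Variance of change: 2σ²(1 − r).
- Residual variance in ANCOVA: σ²(1 − r²).
- Ratio: 2(1 − r)/(1 − r²) = 2/(1 + r).

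The ratio is 1.54 at r = 0.3, 1.33 at 0.5 and 1.18 at 0.7.

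**3. Unequal variances.** With baseline SD s, slope b and ANCOVA residual variance v, the ratio is 1 + (1 − b)²s²/v. It exceeds 1 whenever b is not 1. Setting s = σ, b = r and v = σ²(1 − r²) returns 2/(1 + r). Truncating baseline at 4 reduces s, and with it the loss. A simulation on a 0–15 scale with selection at 4 or more (beta-binomial scores, assumed) had baseline SD 2.2–3.0, follow-up SD 2.9–4.1 and slope 0.34–0.79. The ratio was 1.05 to 1.26. The equal-variance figures in step 2 may therefore overstate the loss in this population.

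**4. What this means for power at 63 per group.** Equal variances, normal approximation:

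| r | 0.5 in score SDs: change / ANCOVA | 0.5 in change SDs: change / ANCOVA |
|---|---|---|
| 0.3 | 66% / 84% | 80% / 94% |
| 0.5 | 80% / 90% | 80% / 90% |
| 0.7 | 95% / 98% | 80% / 86% |

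With 0.5 in score SDs, the numbers per group needed for 80% power (change / ANCOVA) are 88 / 58, 63 / 48 and 38 / 33. With 0.5 in change SDs, the change test needs 63 at every r, and ANCOVA needs 41, 48 and 54.

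**5. Effect of stratifying on baseline.** Take a normal baseline with SD 1, split at the median for randomisation. The cut-point is an assumption, because the article gives none. The baseline variance left within strata is 1 − 2/π = 0.363. The true variance of the change contrast is then proportional to 0.363(1 − r)² + (1 − r²), while the unadjusted test uses 2(1 − r).

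- r = 0.3: 1.088 against 1.400. The standard error is too large by √(1.400/1.088) = 1.134, and type I error is 2.6%.
- r = 0.5: 0.841 against 1.000. Factor 1.091, type I error 3.3%.
- r = 0.7: 0.543 against 0.600. Factor 1.051, type I error 3.9%.

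Simulation with 126 participants and 20,000 runs per setting gave 2.6%, 3.2% and 4.1%, with ANCOVA at 5.0% to 5.1%. The unadjusted test is therefore conservative.

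**The case against.** The strongest objections, and what stands of each:

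- **The power calculation may fit the test exactly.** A reader might infer from step 4 that the trial is underpowered for its primary test. The article does not support that. The stated outcome is change, so reading 0.5 in SDs of change is natural, and the test then has the planned 80%. A shortfall needs both 0.5 in score SDs and r below 0.5, and the article gives neither. This objection stands.
- **Baseline GDS-15 is not left out.** It enters the mixed model as the first outcome value and the planned ANCOVA as covariate. This stands: the point is only that the usual interaction test does not condition on it.
- **The parameterisation is not stated.** A mixed model with a common baseline mean also tests a time × group term and would be about as efficient as ANCOVA. The published sentence does not exclude it. This stands as a condition on the verdict, and the wording should settle it.
- **A condensed article need not list every model term.** For the main model, the absence of gender and stratum is silence and is not an error in itself. Nothing in the article shows that gender predicts change in GDS-15, so no loss from omitting gender is demonstrated. The order of the two analyses, however, is stated.
- **The mixed model was chosen to handle missing values.** That is a sound reason, but a common-baseline mixed model serves it equally well.

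**Conclusion.** The concern holds as a loss of precision. If the mixed model has free group and time main effects, the primary test is a change-score comparison. Its variance is 18% to 54% above that of ANCOVA for assumed r of 0.7 to 0.3 under equal variances, and about 5% to 26% above it in the simulation with selection at 4 or more. Both ranges rest on assumptions, because the article gives no correlation or SD; the second range reflects the entry criterion.

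The analysis is valid. Randomisation keeps the estimate unbiased, and stratification on GDS score makes the unadjusted test conservative, so there is no inflation of type I error. No mismatch with "63 participants are required per group" is shown; what can be said is that the SD behind 0.5 is not stated. Baseline adjustment would raise power at the planned size under either reading of 0.5.

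**What to change.** Make the primary analysis the between-arm difference in post-intervention GDS-15, adjusted for baseline GDS-15 and the randomisation factors (gender and GDS stratum). Two routes serve:

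- a mixed model with a common baseline mean in both arms and an unstructured covariance over the two visits, which keeps the wanted handling of missing follow-up; or
- the ANCOVA already planned, with the randomisation factors added.

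Keep the unadjusted time × group test as a sensitivity analysis. In the Sample size section, state whether 0.5 is in SDs of the score or of the change; if it is in score SDs, give the assumed r as well.

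The cost is wording only. GDS-15 and sex are already collected, and the stratum is known from randomisation. No extra participants or visits are needed.
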